### Statistical methods

Means, standard deviations and frequencies will be used to describe the number of attended visits at the venereology unit with a randomization code (sjekkdeg.no web app users), as well as the absolute number and percentage of visits (new visitors and returning visitors), and the time spent in every educative component among web app users in both groups, after one year of the start of the project.

T-tests will be used to compare the number of appointments attended by users in both groups; and also to compare the number of sjekkdeg.no visitors (new visitors and returning visitors), and the time spent in every educative component among users in Group A versus Group B.

Data will be analysed using the Statistical Package for the Social Sciences (SPSS version 22).

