### Sample size

The web app www.sjekkdeg.no has been running for more than one year and has had, so far, more than 800 unique visitors from Tromsø. We expect the use of the web app to increase further, as it gradually becomes more known. This allows us to assume that one year will be enough to conduct the study and have 1000 visitors.

If 1000 www.sjekkdeg.no users are randomized into the two groups, Group A and Group B, and approximately half of the users in Group A attend an appointment, we can detect a 20% change in the appointment rate (with beta = 0,80 and alpha = 0,05). If the number of appointments attended by users in Group A is lower than expected, the difference between the groups must be larger for us to detect it. With a 30% attended appointments rate in Group A, we still have power to detect a 30% difference between the groups (with beta = 0,80 and alpha = 0,05).

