### Randomisation

The users from Tromsø will be randomized either to the Group A, or to Group B, with a 1:1 allocation ratio (See the study flowchart in Figure 3). Simple randomization will be used. The random allocation sequence will be generated automatically using Google Analytics randomizer code.

Web app users and health professionals are not blinded.

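### Outcome, sample size and primary test use three different quantities: the t-test on appointments attended is given no unit or denominator, so nothing ties it to the attendance rate the trial was sized on

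*Protocol article*

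**What the plan says.** Three sections of the protocol article bear on the primary comparison.

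- **Primary outcome.** The outcome is a number of consultations. The comparison is the total for Group A against the total attended through the appointment system for Group B, over one year. For Group A, attended visits of users who show a control code are entered in a grid. The grid is described for control codes only.
- **Sample size.** The calculation is about a proportion of randomised people. With 1000 users randomised in all, it supposes that "approximately half of the users in Group A attend an appointment" and claims power for a 20% change from that level. A second scenario takes 30% attendance in Group A and a 30% difference.
- **Statistical methods.** Means, standard deviations and frequencies are to "describe the number of attended visits at the venereology unit with a randomization code". Then "T-tests will be used to compare the number of appointments attended by users in both groups".

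T-tests are also planned "to compare the number of sjekkdeg.no visitors (new visitors and returning visitors"), and for time spent in each educational component.

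**The concern.** A t-test needs one value per independent unit and a defined set of units. The article gives neither for its primary test. If the analyst follows the Primary outcome section, there is one number per arm and no within-arm variance. If the analyst uses the clinic data the article describes, which are attended visits carrying a code, everyone in the data set has attended, so attendance itself is not being compared. Only a reading that returns to all randomised users matches the basis on which the trial was sized.

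The main objective is whether online booking improves access to care. Totals without a denominator, or data on attenders alone, cannot show that. Users are anonymous, so if the number allocated to each arm is not kept, the denominator may not be recoverable later.

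The web-use comparison has a related flaw. Under Participants, a user consents, states location and is randomised before seeing either version. How many new visitors fall in each arm is therefore decided by the randomiser.

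**Working it through.** **Inputs.** From Sample size: 1000 users, attendance 50% or 30% in Group A, changes of 20% and 30%, alpha 0.05, and 0.80 printed as beta, read here as power. From Randomisation: 1:1, hence about 500 per arm. Assumed because not stated: a two-sided test, and relative changes (50% to 60%, 30% to 39%).

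**1. The plan's own figure.** Two-proportion formula, with p̄ the mean of p1 and p2:

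n per arm = [1.960·√(2p̄(1−p̄)) + 0.842·√(p1(1−p1) + p2(1−p2))]² / (p2−p1)²

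- 50% v 60%: (1.379 + 0.589)² / 0.10² = 387.3, so 388 per arm (776 in total).
- 30% v 39%: (1.318 + 0.563)² / 0.09² = 436.8, so 437 per arm (874 in total).

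Power at 500 per arm:

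- 50% v 60%: Φ[(0.10·√500 − 1.379)/0.700] = Φ(1.22) = 0.89.
- 30% v 39%: Φ[(0.09·√500 − 1.318)/0.669] = Φ(1.04) = 0.85.

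The smallest relative increases detectable at 80% power are 17.6% and 28.0%. The plan's figures are not reproduced exactly but err on the safe side. They describe attended yes/no over all randomised users.

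**2. Reading A: one total per arm.** Degrees of freedom = 1 + 1 − 2 = 0. A t-test of, say, 250 against 300 returns no p-value.

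**3. Reading B: attended visits with a code only.** If each attender comes once, every value is 1, the variance is zero and the test is undefined. To allow repeat visits, assume visits per attender = 1 + Poisson(0.2) in both arms. The mean is then 1.2 in each arm whatever the attendance rates, so the true difference being tested is zero. In 10,000 simulated trials with 500 per arm, the test rejected in 4.9% (50% v 60%) and 5.1% (30% v 39%). That is the alpha level.

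**4. Reading C: all randomised users, zero for non-attenders.**

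- *Attended yes/no.* A t-test on 0/1 values and a two-proportion test gave the same simulated power, 0.89 and 0.85. Across separate simulations the range was about 0.84 to 0.89.
- *Visit counts, same repeat-visit assumption.* Mean = 1.2p. Variance = 1.64p − (1.2p)², because E(V²) = 0.2 + 1.2² = 1.64.
  - 50% v 60%: means 0.60 and 0.72, SE = √((0.460 + 0.466)/500) = 0.0430, ratio 2.79, power Φ(2.79 − 1.96) = 0.80.
  - 30% v 39%: means 0.36 and 0.468, SE = √((0.362 + 0.421)/500) = 0.0396, ratio 2.73, power Φ(2.73 − 1.96) = 0.78.
  - Simulation gave about 0.79 and 0.77, with type I error about 0.05.

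**5. New visitors.** With simple 1:1 randomisation of N users, the number in Group B is binomial (N, 0.5) whatever the app does. At N = 1000 the expectation is 500 and the standard deviation √(1000·0.25) = 15.8. A test of this count checks the randomiser. Returning visits and time spent can differ by arm and are not affected by this argument.

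**The case against.** The best defence is that the sentence can be read in the valid way. It speaks of users in both groups, and the groups are the randomised arms. The sample size counts randomised users. On that reading each user contributes a number of visits, mostly zero or one, repeat visits are summed within the person, and the test has close to the 80% power claimed. The phrase about a randomisation code stands in the descriptive sentence, where it may only identify which clinic visits belong to trial users. A record of visits supplies a numerator and need not define the analysis population.

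Much of this stands. A reader might infer that the planned test is bound to be either impossible or an answer to another question. The article does not support that, because Reading C is neither stated nor excluded. Nor is the t-test itself at fault: at 500 per arm it is practically the same as a two-proportion test on yes/no data. Nor can one say that all attenders are recorded in the grid, since it is described for Group A codes only.

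What does not stand is leaving the matter to a fuller document. The article does not leave the primary comparison open. It states a comparison of totals, a sample size on a proportion and a named test, and the three do not agree. The new-visitor point concerns a secondary outcome and adds no weight to the primary one, but it is correct for first-visit counts.

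**Conclusion.** The concern holds as an inconsistency in the stated primary analysis: the outcome is a total, the sample size rests on a proportion, and the test has no unit or denominator. Depending on how the sentence is read, the same plan gives no p-value (totals), about 5% rejection under real differences of 50% v 60% or 30% v 39% (coded visits only), or power of about 0.77 to 0.79 (counts) or 0.84 to 0.89 (yes/no) over all randomised users. The stated power therefore applies only to a reading the text does not specify.

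The 0 degrees of freedom need no assumption. The 5% figure assumes the same repeat-visit distribution in both arms, and the power on counts assumes 1 + Poisson(0.2) visits per attender. The article gives no data on repeat visits. The yes/no power assumes a two-sided test, relative effects and 500 users per arm.

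**What to change.** Reword the Statistical methods paragraph along these lines:

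- **Primary analysis.** Among all consenting Tromsø users randomised to each arm, compare the proportion with at least one attended consultation within the year. The denominator is the number allocated to each arm, kept from the app log. Non-attenders count as zero. Users from outside Tromsø, whom the Participants section places in Group A without randomisation, are not in the denominator. Report the risk difference with a 95% confidence interval from a two-proportion test.
- **Supportive.** Consultations per randomised user, zeros included.
- **Web use.** Drop the between-arm test of new-visitor counts and compare the proportion of randomised users who return.

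Align the Primary outcome section with this wording. The particular test is a matter of preference. What must be fixed is the unit, the denominator and the handling of non-attenders.

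The cost is one reworded paragraph, a retained allocation count, and the number of consultations moving from primary to supportive. If the trial team prefers to keep the count as primary, stating the same denominator with zeros would also give a valid test, at somewhat lower power under the visit model assumed above. No extra participants are needed.

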## Methods/Design

### Trial design

To assess the impact of the game-based appointment system, an A/B testing methodology is used. Two versions of the web app, www.sjekkdeg.no, will be used for the A/B test to explore the user interactivity with the site. Version A (control), consisting of the educative web app only; and Version B, which will additionally include a game-based appointment system. Users will be randomly selected to use one of the two versions of the web app. Thus, we will be able to assess which version better supports the typical user in tasks such as booking an appointment at the hospital venereology unit.

The novel game-based appointment system is integrated in the already existing web app www.sjekkdeg.no [10], a game-style web app on sexual health education including social media, targeting North-Norwegian youth, accessible through laptops, smartphones and tablet computers [10]. Gamification techniques [19] such as avatars, achievement-based gifts and social network sharing buttons have been implemented in www.sjekkdeg.no. The web app, which was launched at the end of 2012, seems to be a promising way to encourage users to learn more about sexual health, judging from preliminary visitor returning rates, the average pages visited and the time spent on it [19]. The data also show that the symptom checker is one of the most visited components of the web app [19].

The new game-based appointment system, made available to the users that have been randomized to the intervention group, is based on an automatic prioritization algorithm, which provides the opportunity to book an appointment online. Once randomized to the intervention group, a virtual doctor will ask questions concerning the symptoms that the avatar has experienced. According to the avatar’s answers, the virtual doctor suggests a possible diagnosis or, if a diagnosis is not possible, that the avatar should attend the clinic to be tested for STDs. The appointment system service will be available 24/7, from 1^st^ January 2015 until 31^st^ December 2015.

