### Participants

The web app www.sjekkdeg.no is of free use, and accessible to everyone, although only the users from the city of Tromsø are eligible to participate in this study.

Once a user accesses the web app www.sjekkdeg.no, an informed consent appears on the screen. If the user agrees to participate in the research project, then, a question asking his/her location will appear, as follows: “All the content on this web app is completely anonymous. For research purposes, we only would like to know if you are from Tromsø.” There are two possible answer-options: “Yes, I am from Tromsø”; or “No, I am not from Tromsø”. Users selecting the option “No, I am not from Tromsø” will be immediately selected for the Group A or control group (i.e., the educative web app, without the game-based appointment system). Users answering, “Yes, I am from Tromsø” will be randomized either to the Group A, or to Group B (educative web app, including the game-based appointment system), with a 1:1 allocation ratio (See the study flowchart in Figure 3).

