#### Secondary outcomes

Secondary outcomes are: 1) the impact of the game-based appointment system on how the users utilise the web app www.sjekkdeg.no; 2) the potential benefit for health professionals (doctors and nurses) from such a system through reduced consultation times due to previously acquired information by the symptom checker; and 3) the potential benefit for the users from this game-based appointment system by reducing the booking time threshold of a consultation at the venereology department at the hospital.

On the impact of the game-based appointment system on how the users utilise the web app www.sjekkdeg.no, we expect that the number of visits to the educative components of sjekkdeg.no will increase, after the implementation of the game-based appointment system functionality. And also, we expect that the number of visits to the educative components of sjekkdeg.no will be higher in the appointment group when compared to the control group.

To assess if the game-based appointment system increases the number of visits to the educative components of the web app www.sjekkdeg.no, we will analyse and compare the absolute number and percentage of visits (new visitors and returning visitors) of users in Group A versus Group B after one year of the start of the project. The total number of visitors, as well as the number of new and returning visitors, included in both randomization groups, using the web app, and all of its components, will be tracked through the web analytics tool Google Analytics.

Regarding the potential benefit for health professionals (doctors and nurses) from such a system; we expect that health professionals will be satisfied by having reduced consultation times due to previously acquired information by the symptom checker. To assess if health professionals (doctors and nurses) can benefit from such a system (e.g. through reduced consultation times), a qualitative approach consisting of an *ad hoc* questionnaire based on the Technology Acceptance Model [20], will be used.

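### The planned A-versus-B test on the app-wide number of new visitors can only reflect the 1:1 allocation, not an effect of the appointment system

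*Protocol article*

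**What the plan says.** The first secondary outcome in the protocol article is the system's impact on how people use the web app. For it, Secondary outcomes states that "we will analyse and compare the absolute number and percentage of visits (new visitors and returning visitors) of users in Group A versus Group B". It then names the counts to be tracked with the analytics tool: "The total number of visitors, as well as the number of new and returning visitors, included in both randomization groups", for the app and for its components. Statistical methods turns this into a test: t-tests on appointments attended, and "also to compare the number of sjekkdeg.no visitors (new visitors and returning visitors"), Group A against Group B.

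Three other places fix the order of events:

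- Participants: "Once a user accesses the web app www.sjekkdeg.no, an informed consent appears on the screen". The location question follows, and those who say they are from Tromsø "will be randomized either to the Group A, or to Group B".
- Randomisation: allocation is "with a 1:1 allocation ratio (See the study flowchart in Figure 3). Simple randomization will be used".
- Trial design: the appointment system is "made available to the users that have been randomized to the intervention group".

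**The concern.** An outcome can show an effect of treatment only if it can change after allocation. Being a new visitor is settled by arriving at the site, and arrival comes before allocation. Within the randomised population, the number of new visitors in an arm is simply the number of people allocated to it. The same holds for the number of distinct visitors, which is the natural reading of the total number of visitors in each randomisation group.

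A test on that number checks the randomiser. A non-significant result says nothing about the appointment system, and a significant one would be a chance imbalance in arm size. Because the article presents this count as part of the evidence on use of the app, either result could be misread.

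**Working it through.** **The plan's own figure.** None is given for this comparison. The Sample size section concerns the appointment rate, and only its total of 1000 randomised users is used here.

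**Inputs.** N = 1000 (Sample size); simple 1:1 allocation (Randomisation); consent, location question, then allocation (Participants); appointment system available only after allocation to B (Trial design). Two-sided alpha of 0.05 is assumed, because the article gives 0.05 without sidedness. For contrast, a return probability of 30% in Group A is assumed, with a B-to-A ratio of 1.0, 1.3 or 2.0. The article gives no return rates.

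**Step 1: distribution of the new-visitor count.** Each arriving Tromsø user who consents goes to B with probability 0.5, so

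- nB ~ Binomial(1000, 0.5), with mean 500 and SD = √(1000 × 0.5 × 0.5) = √250 = 15.8;
- the central 95% range for nB is 469 to 531;
- nB − nA = 2nB − 1000, with SD = 2 × 15.8 = 31.6, so the 95% range is ±1.96 × 31.6 = ±62.

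No term depends on what Version B does. If B users brought in friends through the sharing buttons, N would rise, but the newcomers would also be split 1:1 and the expected difference would stay at zero.

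**Step 2: what a test on that count does.** In 20,000 simulated trials per scenario, an exact 50:50 test on new visitors was set beside a two-sided z-test (equivalent to chi-square) on the share of randomised users who return.

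| Return ratio B/A | Test on new visitors rejects | Test on share returning rejects |
|---|---|---|
| 1.0 | 4.8% | 4.8% |
| 1.3 | 4.7% | 85% |
| 2.0 | 4.8% | 100% |

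The first column of results stays flat, so power equals alpha. The second responds to the effect.

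**Step 3: check of the 85%.** For 30% versus 39% with 500 per arm, the pooled proportion is 0.345.

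- SE under the null = √(0.345 × 0.655 × 2/500) = 0.0301.
- SE under the alternative = √((0.30 × 0.70 + 0.39 × 0.61)/500) = 0.0299.
- Power = Φ((0.09 − 1.96 × 0.0301)/0.0299) = Φ(1.04) = 0.85.

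**Step 4: does the unit of the t-test rescue it?** The article does not state the unit. One count per arm has no within-arm variance. Per randomised user, being a new visitor equals 1 for everyone, so again there is no variance. Per day or week, a t-test can be computed, but the expected count is the same in both arms in every period, whatever the system does.

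**The case against.** The strongest reply is that the new-visitor count is one part of a wider comparison, and that the rest is sound. Most of this stands.

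- **Total visits.** A reader might infer that total visits are also fixed by allocation. They are not. If each user who returns does so once, 500 per arm gives expected totals of 500 × 1.30 = 650 and 500 × 1.39 = 695 at a return ratio of 1.3, so the total responds.
- **Power and error rate for total visits.** A reader might also infer that testing total visits loses power or inflates the error rate. That would follow only from treating the two arm totals as Poisson counts, a test the article does not name. It names t-tests. With visits per user as the unit, each first visit adds a constant 1 to every user and leaves the t statistic unchanged. The documents support no loss figure of this kind.
- **Components.** Secondary outcomes tracks visitors to each component as well as to the app. Whether a first-time user opens a given component is decided after allocation and can differ by version, so those counts are informative.
- **Percentages.** The percentage of new visits carries the same information as the percentage of returning visits. In the example above it falls from 1/1.30 = 76.9% in A to 1/1.39 = 71.9% in B.
- **Other measures.** The article already expects a higher return rate in B and plans to compare time spent, so misreading of a null on new visitors is a risk and not a certainty.

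None of this repairs the app-wide new-visitor comparison. It is a stated analysis and not a detail left to a fuller plan.

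**Conclusion.** The point holds for the app-wide number of new or distinct visitors among randomised users, and only for that. Its distribution is Binomial(N, 0.5) under any effect. With N = 1000 the difference between arms ranges over about ±62 by chance, and a test on it has power equal to its alpha of about 5%. The count is not literally fixed, since simple randomisation lets it vary; what the intervention cannot change is its distribution.

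This rests on the stated order of arrival, consent, location question and allocation, and on counting randomised Tromsø users only. Participants places users from elsewhere in Group A without randomisation. If they entered the count, Group A would be larger because of the catchment, which is still not an effect of the appointment system. The 85% and 100% in the working depend on assumed return rates and serve only as contrast.

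Severity is minor. The primary outcome is untouched, and the secondary outcome on use remains answerable from the other planned measures.

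**What to change.** In Secondary outcomes and Statistical methods, remove the app-wide number of new or distinct visitors as an A-versus-B outcome, and report it as participant flow: the number allocated to each arm. Base the comparison of use on randomised Tromsø users, with all users allocated to the arm as denominator:

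1. the proportion who return at least once, as a risk difference with 95% CI and a chi-square test;
2. the number of visits to the educative components per randomised user, counting zero for those who open none, by t-test or a negative binomial model.

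The cost is a change of wording in two sections and an analytics export by randomisation group, with the number allocated alongside. No further users and no new data items are needed, because returning visitors and component visits are already to be tracked. The downside is that new-visitor counts become descriptive only.
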